#### 2) Progression-free survival (PFS)

Calculated as the number of days from the enrollment date as the start date to the date on which exacerbation is determined or to the date of death due to any cause, whichever is earlier.

- “Progression” includes both PD (progression) based on the imaging exam in “11.1.10. Best overall effect” and exacerbation (progression) of the underlying disease (clinical exacerbation) that cannot be confirmed by an imaging exam. The date on which the imaging examination was performed is taken as the exacerbation date if the exacerbation is determined based on the imaging exam, and the clinical judgment date is taken as the exacerbation date in the case of clinical exacerbation. If the tumor size becomes extremely small, etc., a determination of PD will be made according to the criteria for determining efficacy, but even if it is clinically judged as “apparently not exacerbated,” a determination of PD according to the efficacy criteria will have priority (in this case, whether or not to continue administration of the study drug will prioritize the clinical judgment). Moreover, even if a determination of PD is not made according to the criteria for determining efficacy, if there is a clear judgment of clinical exacerbation, the

clinical judgment is given priority.

- In surviving cases that are not determined to be exacerbation, the case is terminated on the last day (the date of final confirmation of progression-free survival) when there is no clinical exacerbation (confirmed progression-free by image inspection and specimen inspection is not mandatory, and a confirmation of clinical non-progression can be made in an outpatient clinic, etc. Telephone communication only is not acceptable. If information about exacerbation or no progression is obtained during a hospital transfer or a medical institution referral, etc., the document(s) providing the medical information that describe the basis of the diagnosis must be received and retained. In this case as well, telephone contact only is not acceptable).
- Events and terminations are treated the same as in the case of chemotherapy discontinuation due to reasons such as toxicity or patient refusal, etc., and also when another treatment is added as a post-treatment. In other words, the case is not terminated at the time when treatment is discontinued or on the day that the post-treatment starts.
- When the diagnosis of exacerbation is based on imaging diagnosis, the event is not the exam date for "suspicion based on imaging" but rather the "exam date" for an imaging exam for which "confirmation" is obtained at a later date. If the case is determined to be clinically exacerbated regardless of diagnostic imaging, the event is considered to be the day on which the case is determined to be exacerbated.
- The occurrence of secondary cancer (including metachronous double cancer and metachronous multiple cancer) is neither an event nor a termination, and it is considered as progression free survival until other events are observed.

### 3) Disease control rate

The proportion of patients within the FAS not classified as PD or NE in "11.1.10. Best overall effect" as determined by the facility.

### 4) Incidence of adverse events

Percentage of patients who developed each adverse event in SAS.

In addition, the frequency of the worst grade according to CTCAE v5.0-JCOG is determined for each adverse event.

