#### 7.2.1. Grading adverse events

When grading adverse events, each event is given the grade closest to the defined grades 0–4. In addition, if a specific treatment is described for a grade, grade it based on its clinical necessity. For example, when the patient's pleural fluid is increasing and the patient refuses oxygen inhalation and chest drainage despite these being indicated in this situation. In these cases, the grade should be assigned based on the medical determination of what should be done, not what was actually done.

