## 8.3. Tests and evaluations during the protocol treatment period

### 8.3.1. Safety endpoints

In this study, protocol treatments are carried out with various medicines, so there is no uniform safety endpoint, but the patient's safety is evaluated with due consideration by the doctor in charge according to the description in the respective drug package insert, and tests are conducted as appropriate. The evaluations are based on "7.2 Evaluating adverse events/adverse reactions," and when they correspond to "10.1 Serious adverse events and events subject to emergency reports" they are reported to the Study Representative Physician according to "10.2 Requirements and procedures for reporting to the Study Representative Physician." Otherwise, enter into the EDC the worst grade  $\geq 2$  adverse events that have occurred from the start of treatment to 30 days after treatment discontinuation or the date of subsequent treatment initiation, whichever comes first. And the assessment of them to 30 days after treatment discontinuation or the date of initiation of subsequent treatment, whichever comes first. If adverse events are considered to be related to protocol treatment or they are severe regardless of relation to protocol treatment, follow-up will be continued as long as possible until the adverse event is considered resolved, resolved, or stable.

※Instruction of safety information shall be in accordance with the separately specified procedures.

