#### 8.4. Tests and endpoints when the protocol treatment is completed

Record the following information if treatment is discontinued.

- Treatment discontinuation date (the date when it was determined that the protocol treatment was to be discontinued), and the reason for discontinuation
- Adverse events between the start of treatment and within 30 days after treatment was completed
- Imaging exam for tumor evaluation

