### 12.3.3. Analysis of safety secondary endpoints

Among the secondary endpoints, the safety endpoints are the incidence of adverse events. The safety analysis set is SAS for each drug cohort, and analysis for each drug cohort is performed at the time of main analysis or at the time of additional analysis of the primary endpoint thereafter. The frequencies of the worst grade for each adverse event are summed when estimating the incidence of adverse events. An accurate method (Clopper and Pearson method) based on a binomial distribution is used for 95% confidence interval estimates of the incidence. Furthermore, the safety in the FAS is to be analyzed as needed.

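### The adverse event endpoint has no grade limit, but routine events below grade 2 are not entered in the EDC, so the reported incidence will understate any-grade incidence

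*Protocol*

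**What the plan says.** **Endpoint.** Section 12.2.2 4) defines adverse event incidence as "Percentage of patients who developed each adverse event in SAS". It adds that "the frequency of the worst grade according to CTCAE v5.0-JCOG is determined for each adverse event". No minimum grade and no time window are given.

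**Analysis.** Section 12.3.3 states: "The frequencies of the worst grade for each adverse event are summed when estimating the incidence of adverse events". It continues: "An accurate method (Clopper and Pearson method) based on a binomial distribution is used for 95% confidence interval estimates of the incidence". Again there is no grade limit.

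**Grading.** Under section 7.2.1, "each event is given the grade closest to the defined grades 0–4", so grade 1 is a category in use.

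**Collection.** Section 8.3.1 first sends events that meet the section 10.1 criteria through the reporting route. For the rest it says: "Otherwise, enter into the EDC the worst grade $\geq 2$ adverse events that have occurred from the start of treatment". The window ends 30 days after discontinuation or at the start of the next treatment, whichever is earlier. Note *7 to the study calendar (section 8.6) gives the same window but no grade threshold.

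**Record at discontinuation.** Section 8.4 lists "Adverse events between the start of treatment and within 30 days after treatment was completed". It has neither the grade threshold nor the cut-off at subsequent treatment.

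**Other routes for grade 1 events.** Section 10.1 3) requires a report of unexpected grade 1 to 3 events that need hospitalization, or its prolongation, of at least 24 hours. Section 7.2 has laboratory abnormalities in the paediatric grading table, for children under 15, recorded on the eCRF adverse event form with no grade floor.

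**The concern.** The endpoint asks how many patients had each adverse event at any grade. The collection rule supplies that answer only from grade 2 upward. For ordinary events, a patient with grade 1 and a patient with no event look the same in the database, so the bottom of the worst-grade distribution is missing and the summed incidence is too low if it is read as any-grade.

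An analysis plan cannot repair this, because it cannot recover data that the protocol does not ask sites to enter. The endpoint, its analysis and the collection rule all stand in the protocol and disagree there.

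What is at stake is the meaning of the only safety endpoint. Section 2.3.1 lets companies that supply drug free of charge receive the safety data, section 13.6 3) has adverse events reported to the Ministry, and section 13.3.10 foresees research data supporting later trials or the off-label study group. A table titled as the endpoint is now worded could be set beside any-grade figures from elsewhere and look more favourable than it is.

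**Working it through.** The protocol states no figure on this point, so there is nothing to reproduce. The check is a comparison of sections, followed by an illustration.

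**Step 1: what reaches the incidence count**

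| Worst grade of an event in a patient | Entered under 8.3.1? | Needed for 12.2.2 4) and 12.3.3 as worded? |
|---|---|---|
| 2 or higher, outside the emergency route | Yes | Yes |
| 1, ordinary event | No | Yes |
| 1, unexpected and needing hospitalization | Reported under 10.1 3) | Yes |
| 1, listed laboratory abnormality, age under 15 | Adverse event form under 7.2, no floor stated | Yes |

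The second row is the gap. The last two rows are narrow exceptions that do not supply routine grade 1 data. If those records entered the table, the effective threshold would differ between patients, by age and by hospitalization.

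**Step 2: size of the understatement**

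Let n be the number of patients in the safety set, a the number with worst grade 2 or higher for an event, and b the number with worst grade 1 who are captured by no other route.

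- Reported incidence = a/n
- Any-grade incidence = (a + b)/n
- Understatement = b/n
- With s = b/(a + b), reported incidence = any-grade incidence × (1 − s)

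**Step 3: illustration**

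Inputs: n = 80, from 50 patients with and 30 without measurable lesions (sections 0.5 and 12.6); section 12.7.1 2) uses the same denominator. The values of a and s are assumptions, because the protocol gives no grade distribution.

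Take a = 8. Reported incidence is 8/80 = 10.0%, exact 95% CI 4.4% to 18.8%.

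| Assumed s | a + b = 8/(1 − s) | Any-grade incidence (95% CI) | Inside 4.4% to 18.8%? |
|---|---|---|---|
| 0% | 8 | 10.0% (4.4% to 18.8%) | Yes |
| 25% | 10.7, rounded to 11 | 13.8% (7.1% to 23.3%) | Yes |
| 50% | 16 | 20.0% (11.9% to 30.4%) | No |
| 75% | 32 | 40.0% (29.2% to 51.6%) | No |

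A second case: a = 16, so reported incidence is 16/80 = 20.0%, CI 11.9% to 30.4%. If a further 10% of patients have grade 1 only (b = 8), any-grade incidence is 24/80 = 30.0%, just inside the interval. If a further 30% do (b = 24), it is 40/80 = 50.0%, well outside.

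**Step 4: window**

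Section 8.3.1 and note *7 agree on the earlier of 30 days after discontinuation and the start of subsequent treatment. Section 8.4 gives 30 days with no such limit. Sections 12.2.2 4) and 12.3.3 give no window, so they do not settle which applies. The two differ only for patients who start another treatment within 30 days.

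**The case against.** The best defence is that collecting only grade 2 or worse is a legitimate way to limit site burden, that section 8.3.1 states the threshold openly under a safety endpoint heading, and that table titles and footnotes normally belong to an analysis plan or report. All of that stands as far as it goes. The threshold itself is not criticised, and nothing in the protocol says that the tables will be labelled any-grade. But the limit is missing from the endpoint definition and from its analysis, and those are in this document.

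It can also be said that section 8.4 and note *7 carry no grade floor, so grade 1 events might be recorded after all. That would give the protocol two collection rules rather than one. Section 8.3.1 is the one that says specifically what to enter, and the sections need reconciling on either reading.

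Three stronger conclusions that a reader might draw are not supported:

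- **That every grade 1 event is lost.** Sections 10.1 3) and 7.2 provide for some.
- **That the confidence interval must exclude the any-grade rate.** It does so only when enough affected patients have grade 1 alone. At 16/80 the interval still contains 30%, and at 10/50 (10.0% to 33.7%) it does too.
- **That safety oversight is weakened.** Section 12.7.1 2) acts on treatment-related deaths and the serious adverse event profile, and urgent reporting to the authorities in section 10.3.2 concerns deaths, grade 4 events and unexpected serious events. None of these depends on routine grade 1 rates.

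**Conclusion.** The point holds as a mismatch between a stated endpoint and the data collected for it. Followed as written, the protocol cannot deliver the incidence of each adverse event at any grade, nor a complete worst-grade distribution. What it can deliver is the incidence of grade 2 or worse, with a few grade 1 records from two side routes.

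The understatement against any-grade incidence equals the share of patients whose worst grade is 1 and who are captured by neither route. The documents do not give that share, so its real size is unknown; the range in the illustration, from none to fourfold, rests wholly on the assumed share. The window discrepancy in section 8.4 is secondary.

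The endpoint is descriptive, with no test or threshold attached. The primary endpoint is untouched. The correction should be made because this is the study's only safety endpoint and its results go to outside parties.

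**What to change.** 1. In sections 12.2.2 4) and 12.3.3, restate the endpoint as the incidence and worst-grade distribution of adverse events of grade 2 or worse in the safety set, within one stated window, and apply the Clopper-Pearson intervals to that quantity.
2. Title the incidence tables to show the grade threshold and the window.
3. State that grade 1 records arising under section 7.2 (children under 15) and section 10.1 3) (unexpected events needing hospitalization) are listed separately and not counted in this incidence, so that one threshold applies to all patients.
4. Reconcile sections 8.3.1, 8.4 and calendar note *7 on both the grade threshold and the end of the window.

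The cost is protocol wording and table titles, with no new data and no recovery of past grade 1 events. The downside is that the endpoint is visibly narrower. Collecting all grades would also remove the mismatch, but it would add data entry and would leave patients already past the window without grade 1 data unless these were recovered, so restating the endpoint is the more practical course.

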## 12.3. Main analysis and judgment criteria

### 12.3.1. Primary endpoint analysis

In this study, the primary endpoint is the response rate based on the best overall effect up to  $16 \pm 1$  weeks after the start of treatment among patients with measurable lesions in the FAS for each drug cohort. This study is not intended to test hypotheses set in advance, but from the viewpoint of feasibility under the patient-proposed healthcare services, with each drug cohort expected to have up to 50 patients who have measurable lesions as subjects. The main analysis will be conducted for each drug cohort when those 50 patients have been enrolled and the 50th patient has completed the efficacy evaluation up to the time point of  $16 \pm 1$  weeks. For patients who were determined to have measurable lesions at the time of enrollment but for whatever reason the determination was changed to no measurable lesions after treatment started, the best overall response is given as NE.

In this study, it is decided to use Bayesian inference, and if the probability that the posterior distribution of the response rate exceeding the threshold response rate of 60% exceeds 95%, it is determined that the medicine can be expected efficacious. If the corresponding drug is provided free of charge by a company, a report is to be prepared summarizing the information on the drug, and the results of the research shared with the corresponding company, which can then explore the pathway to regulatory approval including clinical trials.

We adopt a beta (0.6, 1.4) with an expected value of 30% as the prior distribution.

In line with the above analysis, 95% confidence intervals (two-sided) are also calculated using an accurate method from frequentist theory (Clopper and Pearson method) based on a binomial distribution for the interval estimates of the response rate.

Furthermore, an interim analysis (12.4.) will be conducted according to the separately established policy based on the data from the time of regular monitoring conducted twice a year.

Even if more than 50 eligible patients with measurable lesions can be enrolled, the same analysis and response as for the main analysis will be performed, and an updated version of the Final Report will be created as an additional analysis of the primary endpoint for each 50 patients, and the results will be examined.

### 12.3.2. Analysis of efficacy secondary endpoints

Among the secondary endpoints, the efficacy endpoints are overall survival, progression-free survival, and disease control rate. The efficacy analysis set is the FAS for each drug cohort, and analysis is performed for each drug cohort at the time of main analysis or the subsequent primary endpoint analysis. Survival curves, median survival time, and annual survival rates are estimated for each survival time using the Kaplan-Meier method. The 95% confidence intervals (two-sided) are estimated using the Brookmeyer and Crowley method for the respective median survival times. The 95% confidence intervals (two-sided) are calculated using Greenwood's formula for interval estimation of the annual survival rates. An accurate method (Clopper and Pearson method) based on a binomial distribution is used for interval estimates for the disease control rate.

### 12.3.3. Analysis of safety secondary endpoints

Among the secondary endpoints, the safety endpoints are the incidence of adverse events. The safety analysis set is SAS for each drug cohort, and analysis for each drug cohort is performed at the time of main analysis or at the time of additional analysis of the primary endpoint thereafter. The frequencies of the worst grade for each adverse event are summed when estimating the incidence of adverse events. An accurate method (Clopper and Pearson method) based on a binomial distribution is used for 95% confidence interval estimates of the incidence. Furthermore, the safety in the FAS is to be analyzed as needed.

## 12.4. Interim analysis

According to the appearance of biomarkers, there is a high possibility of difficulties in conducting research which might be caused by the difference between the prior plans and the actual research progress compared to the usual clinical trials, such as the possibility of the prospective accumulation period being uncertain due to the small number of patients. It is a problem from an ethical standpoint that a particularly ineffective treatment might be continued without being stopped by unsatisfactory patient accrual. It is important to incorporate into the research plan a method to deal with the uncertainty and difficulties in conducting the research.

Since the Bayesian design allows a more flexible statistical evaluation than does the hypothesis test of the frequentist theory, in addition to the main analysis in this study, the Bayesian aspect is also monitored in the intermediate analysis.

When  $\geq 15$  patients are enrolled for each drug cohort, response rates based on the best overall response are assessed based on a Bayesian analysis up to  $16 \pm 1$  weeks after treatment during semiannual regular monitoring (14.1 "Periodic monitoring"), and the need for discontinuation due to inefficacy or discontinuation due to efficacy is assessed to determine whether the drug cohort is considered to be continuable.

The information required for discontinuation due to inefficacy or discontinuation due to efficacy is shown in Table 12.4.

We adopt a beta (0.6, 1.4) with an expected value of 30% as the prior distribution relating to response rates in this trial. If the data actually obtained is significantly below or above this prior expectation, the necessity of discontinuation due to inefficacy or discontinuation due to efficacy, respectively, will be considered by using a threshold of 20% as an indication of "much below prior expectation" and a threshold of 60% is set as an indication of "significantly exceeding prior expectations." If the probability of exceeding the 20% threshold is less than 5% when calculating the posterior distribution of the response rate, the necessity of early discontinuation due to inefficacy is examined. Moreover, the probability of exceeding

the 60% threshold is  $\geq 95\%$  when calculating the posterior distribution of the response rate, the necessity of early discontinuation due to efficacy is examined.

If necessary, subgroups by combining drugs with biomarkers and cancer types can also be considered.

**Table 12.4: Decision table for early discontinuation (discontinuation due to inefficacy or discontinuation due to efficacy) in each drug cohort**

| <Denominator>
Number of cases that
can be evaluated for
response | <Numerator>
Number of cases to
consider
discontinuation due to
inefficacy
(The expected value
of the prior distribution
is 30%, and the
maximum number of
response cases in
which the probability
that the posterior
distribution exceeds
the 20% threshold is
less than 5%) |       | <Numerator>
Number of cases to
consider
discontinuation due to
efficacy
(The expected value
of the prior distribution
is 30%, and the
minimum number of
response cases in
which the probability
that the posterior
distribution exceeds
the 60% threshold is $\geq$
95%) |       |
|---------------------------------------------------------------------------|------------------------------------------------------------------------------------------------------------------------------------------------------------------------------------------------------------------------------------------------------------------------------------------------------------------------|-------|--------------------------------------------------------------------------------------------------------------------------------------------------------------------------------------------------------------------------------------------------------------------------------------------------------------------|-------|
| 5                                                                         | -                                                                                                                                                                                                                                                                                                                      | -     | -                                                                                                                                                                                                                                                                                                                  | -     |
| 6                                                                         | -                                                                                                                                                                                                                                                                                                                      | -     | -                                                                                                                                                                                                                                                                                                                  | -     |
| 7                                                                         | -                                                                                                                                                                                                                                                                                                                      | -     | 7                                                                                                                                                                                                                                                                                                                  | 1.000 |
| 8                                                                         | -                                                                                                                                                                                                                                                                                                                      | -     | 8                                                                                                                                                                                                                                                                                                                  | 1.000 |
| 9                                                                         | 0                                                                                                                                                                                                                                                                                                                      | 0.000 | 9                                                                                                                                                                                                                                                                                                                  | 1.000 |
| 10                                                                        | 0                                                                                                                                                                                                                                                                                                                      | 0.000 | 10                                                                                                                                                                                                                                                                                                                 | 1.000 |
| 11                                                                        | 0                                                                                                                                                                                                                                                                                                                      | 0.000 | 10                                                                                                                                                                                                                                                                                                                 | 0.909 |
| 12                                                                        | 0                                                                                                                                                                                                                                                                                                                      | 0.000 | 11                                                                                                                                                                                                                                                                                                                 | 0.917 |
| 13                                                                        | 0                                                                                                                                                                                                                                                                                                                      | 0.000 | 12                                                                                                                                                                                                                                                                                                                 | 0.923 |
| 14                                                                        | 0                                                                                                                                                                                                                                                                                                                      | 0.000 | 12                                                                                                                                                                                                                                                                                                                 | 0.857 |
| 15                                                                        | 0                                                                                                                                                                                                                                                                                                                      | 0.000 | 13                                                                                                                                                                                                                                                                                                                 | 0.867 |
| 16                                                                        | 0                                                                                                                                                                                                                                                                                                                      | 0.000 | 14                                                                                                                                                                                                                                                                                                                 | 0.875 |
| 17                                                                        | 0                                                                                                                                                                                                                                                                                                                      | 0.000 | 15                                                                                                                                                                                                                                                                                                                 | 0.882 |
| 18                                                                        | 1                                                                                                                                                                                                                                                                                                                      | 0.056 | 15                                                                                                                                                                                                                                                                                                                 | 0.833 |
| 19                                                                        | 1                                                                                                                                                                                                                                                                                                                      | 0.053 | 16                                                                                                                                                                                                                                                                                                                 | 0.842 |
| 20                                                                        | 1                                                                                                                                                                                                                                                                                                                      | 0.050 | 17                                                                                                                                                                                                                                                                                                                 | 0.850 |
| 21                                                                        | 1                                                                                                                                                                                                                                                                                                                      | 0.048 | 17                                                                                                                                                                                                                                                                                                                 | 0.810 |
| 22                                                                        | 1                                                                                                                                                                                                                                                                                                                      | 0.045 | 18                                                                                                                                                                                                                                                                                                                 | 0.818 |
| 23                                                                        | 1                                                                                                                                                                                                                                                                                                                      | 0.043 | 19                                                                                                                                                                                                                                                                                                                 | 0.826 |
| 24                                                                        | 1                                                                                                                                                                                                                                                                                                                      | 0.042 | 19                                                                                                                                                                                                                                                                                                                 | 0.792 |
| 25                                                                        | 1                                                                                                                                                                                                                                                                                                                      | 0.040 | 20                                                                                                                                                                                                                                                                                                                 | 0.800 |
| 26                                                                        | 2                                                                                                                                                                                                                                                                                                                      | 0.077 | 21                                                                                                                                                                                                                                                                                                                 | 0.808 |
